##### Facial appearance

Variables measuring nasolabial appearance will be derived from the Asher McDade Index^22^ and variables measuring facial shape and symmetry from data generated from the software from the Vectra H2 3D camera.^23^

##### Hearing and speech

Data from a hearing screen will indicate hearing acuity for each ear at the frequencies 500 Hz, 1000 Hz, 2000 Hz, 4000 Hz, 8000 Hz. A speech and language sample will provide data on ongoing velopharyngeal function and speech sound errors. After the research clinics, two specialist cleft speech and language therapists will carry out consensus listening of the speech samples and rate them following the Cleft Audit Protocol for Speech-Augmented (CAPS-A).^24 25^ The CAPS-A analysis will generate data from which we will create the following variables for statistical analysis:

Intelligibility on a 5-point scale (normal, different from other people’s speech but not enough to cause comment, different enough to provoke comment, but possible to understand most speech, only just intelligible to strangers, impossible to understand).Velopharyngeal composite score on a 3-point scale (competent, marginally incompetent, incompetent).^26 27^Absence/Presence of active cleft speech characteristics in three categories (anterior, posterior, non-oral).Per cent Consonants Correct measure (continuous variable).

##### Dental outcomes and oral health

Dental health will be measured using the sum of the number of Decayed, Missing and Filled Teeth^28^ in the permanent teeth as the standard protocol for measurement of dental caries. A further calculation of decayed and filled teeth divided by the total number of teeth) will be calculated to derive a score, which will assess dental health based on decay, given that many teeth are missing for reasons other than decay in individuals born with CL/P. A variable regarding periodontal health will be obtained from the Community Periodontal Index for Treatment Needs^29^ and the simplified Oral Hygiene Index.^30^

##### Growth

The intraoral scanner will provide data on dental arch alignment. Variables will be derived from data generated from analysis of the scans using the Modified Huddart-Bodenham Index.^31^ Peer Assessment Rating scores will also be obtained.^32^

##### The economic impact of a cleft diagnosis for patients

A variable to measure productivity will be derived from the Work Productivity and Activity Impairment questionnaire,^33^ a 6-item questionnaire measuring the effect of participants’ health problems on their ability to work and perform regular activities. Measures of healthcare resource use will be gathered from the MODular Resource-Use Measure.^34^ This is a questionnaire used to measure participants’ use of healthcare resources over the previous 6 months. We will also ask about the use of private healthcare and about any out-of-pocket expenses they may have had related to their cleft healthcare and postsecondary education (if applicable) in the last 6 months.

### Confounders

Health literacy is an important confounder as it will impact participants’ ability to respond to the self-report questionnaires. This will be measured using the Health Literacy Survey-Q12, a 12-item adapted short form questionnaire of the HLS19-Q47 for measuring general health literacy in general adult populations.^35^

The Revised Life Orientation Test will be used to measure the participants’ outlook and world view; this measure of dispositional optimism could influence their satisfaction scores.^36^

### Data analyses

Descriptive statistics will be used to summarise the exposures (ethnicity, sex, gender, socioeconomic status and geographical location) using frequencies and percentages. For the numerical outcomes, central tendency and variation will be summarised by means and SD or medians and IQRs as appropriate. Categorical outcomes will be summarised by frequencies and percentages.

Regression models will be used to assess associations between the exposures and the primary outcome. Secondary analysis will be based on regression models for each of the other outcomes separately. Linear, logistic, ordinal logistic or Poisson regression will be used to model associations for continuous, binary, ordinal or discrete outcomes, respectively; continuous outcomes will be transformed before analysis if model residuals are skewed.

Directed acyclic graphs will be used to conceptualise associations between variables to enable an appropriate set of confounders to be selected for modelling each exposure-outcome association; age and the other exposures will be considered as potential confounders as well as health literacy and dispositional optimism. All models will be fitted before and after adjustment for appropriate confounders. A sensitivity analysis will be undertaken, whereby all unadjusted models will be repeated, restricting to only those with full confounder information available. This will confirm whether any changes after adjustment are due to missing data or the confounding variables themselves.

Potential cleft centre-level variation for each outcome will be identified through estimation of variance partition coefficients from multilevel models with centre treated as a random effect, adjusting for appropriate fixed effects (eg, age and sex). Any outcomes displaying centre-level variation will be modelled using multilevel rather than single-level models.

Potential effect modification through cleft subtype and/or syndromic status will be tested through inclusion of interaction terms in models; if the exposure-outcome association differs according to the categories of cleft subtype/syndromic status, category-specific regression estimates will be presented.

The economic impact of a cleft diagnosis will be collected through the self-report questionnaire and will be analysed to determine variation in resource use within the sample.

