### Power calculations

A sample of 600 would allow a mean score of 86.4 to be estimated with a 95% CI of 84.2 to 88.6 (mean and SD based on Foo *et al*^8^) for the primary outcome measure (the emotional role subscale of Short Form 36 (SF-36)). With just over 1000 babies born each year with CL/P, the total population available to recruit from over a 2-year period is approximately 7000 (1000 individuals born with cleft each year for ages 18–23—totalling 6000—plus an additional year of recruitment to include young adults who turn 18 during the first year of recruitment). The recruitment rate for a comparable study run by the same team and involving younger children was 75%^9^; therefore, recruiting 600 is achievable. Nevertheless, we propose to over-recruit by 40 (total sample size 640) as contingency for missing data.

To achieve a sample size of 640, we aim to recruit from across the UK’s cleft teams. Some serve a larger population than others, so it is likely that we may recruit more from some sites than others. Our work with young people to date suggests that they would be willing to attend this research clinic. We aim to recruit participants across all groups to ensure that the study sample reflects the general population in terms of ethnicity, socioeconomic status, gender and cleft subtypes. Recruitment will be facilitated through targeted dissemination of study information via general medical practices, dental practices and community organisations serving diverse ethnic groups. Regular evaluation of those recruited will ensure the sample is representative of target population in ethnicity, biological sex, socioeconomic status and geographic location to minimise the risk of selection bias.

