### Derived variables

#### Primary outcome measure

The variable used as the primary outcome measure for this study will be derived from the SF-36.^14^ We will use the five questions of the emotional role subscale of SF-36, also known as Mental Health Inventory. SF-36 was chosen to derive the primary outcome measure following the focus groups held with young adults born with CL/P,^6^ during which it was established that emotional well-being was the primary concern while transitioning into adult care.

The Patient-Reported Outcome Measurement Information System (PROMIS)^15^ Global Health Scale will also be included. This is a standardised psychometric instrument containing 10 questions pertaining to health-related quality of life. The SF-36 emotional role subscale will remain as the primary outcome measure due to its use in calculating the power of the study and for comparison with older literature.

The decision to retain both the SF-36 and the PROMIS, which has been designed to supersede the SF-36, was driven by the desire to compare the results from this study with other studies, which were carried out prior to the development of the PROMIS and which therefore used the SF-36. However, we also want to enable future researchers to compare their results using the PROMIS with our data and using only the SF-36 would limit that ability. In order to reduce repetition within this part of the questionnaire, we limited the questions from the SF-36 to just those five which comprise the emotional role subscale, as the study was designed with these forming the primary outcome measure and the means for calculating the sample size needed to ensure a robustly powered study.

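### The transform-if-skewed rule suits a primary score bounded near its maximum poorly, and plain Poisson is a fragile default for the discrete outcomes

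*Protocol article*

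**What the plan says.** The Data analyses section of the protocol article fixes the model family by type of outcome: "Linear, logistic, ordinal logistic or Poisson regression will be used to model associations for continuous, binary, ordinal or discrete outcomes, respectively". For continuous outcomes it adds one rule: "continuous outcomes will be transformed before analysis if model residuals are skewed". No other response to skewed residuals is given.

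The Power calculations section supplies the only distributional figures for the primary outcome: "A sample of 600 would allow a mean score of 86.4 to be estimated with a 95% CI of 84.2 to 88.6". The SD is attributed to a cited study and is not printed. The Primary outcome measure section defines the score: "We will use the five questions of the emotional role subscale of SF-36, also known as Mental Health Inventory". It does not state the range of the score. It keeps this score as primary because the study was sized on it and because it allows comparison with older literature.

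Of the discrete outcomes, the clearest is DMFT: "Dental health will be measured using the sum of the number of Decayed, Missing and Filled Teeth". The same section notes that people born with a cleft often lack teeth for causes unrelated to caries. No mean, variance or dispersion is given for any count.

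**The concern.** **Primary score.** A mean that close to the top of a bounded scale with so large an SD forces strong left skew, so the residual check would very probably lead to a transformation. That has three drawbacks:

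- The scale of the primary group contrasts would be chosen after the residuals have been seen.
- Those contrasts would leave the score scale on which precision was planned and on which comparison with earlier studies is wanted.
- Skew that comes from people heaped at or near the maximum may survive, because a monotone transformation gives everyone at the top the same new value.

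**Counts.** Model-based Poisson standard errors take the variance to equal the mean. If the variance is larger, they are too small. Differences by ethnicity, sex, socioeconomic status or region would then be declared too often, and such differences are what the study sets out to find.

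**Working it through.** **Inputs.** From Power calculations: n = 600, mean 86.4, 95% CI 84.2 to 88.6, so half-width (88.6 - 84.2)/2 = 2.2. Assumed: a score range of 0 to 100, and that these figures describe the five-question score.

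**1. The plan's own figure.** Half-width = 1.96 × SD/√n, so SD = 2.2 × √600/1.96 = 27.5. Put back, n = (1.96 × 27.5/2.2)² = 24.5² = 600.25, which agrees with the stated 600. Because the SD was solved from the interval, this shows internal consistency only. If the half-width was rounded (2.15 to 2.25), the SD lies between 26.9 and 28.1.

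**2. Distance to the maximum.** u = (100 - 86.4)/27.5 = 0.495. A normal distribution with these values would put 31% of scores above 100.

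**3. Skewness.** With a maximum u SDs above the mean, skewness cannot exceed u - 1/u = 0.495 - 2.022 = -1.53. Over the rounding range of the SD, this limit runs from -1.47 to -1.58. It holds for any item structure.

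**4. Share scoring 90 or more.** On 0 to 100, X(X - 90)/1000 is at most 0 below 90 and at most 1 from 90 upward. Hence P(X ≥ 90) ≥ (E[X²] - 90 E[X])/1000 = (86.4² + 27.5² - 90 × 86.4)/1000 = (7464.96 + 756.25 - 7776)/1000 = 0.445, or about 45%. Over the rounding range of the SD, the bound runs from 41% to 48%.

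The rule refers to residuals, not to the raw score. If the exposures explain a modest part of the variance (assumed), the residuals inherit most of this skew.

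**5. Does a transformation cure it?** That depends on the share at exactly the maximum, which the mean and SD do not fix. With 21 equally spaced levels (assumed: five items of five levels), this share can be as low as 2.6%. For the 21-level shape with the smallest possible largest point mass (30%), a reflected log moves skewness from -2.75 to -0.38. With a proportion p above one half at the top, no monotone transformation brings skewness nearer zero than (1 - 2p)/√(p(1 - p)). So a transformation may or may not work.

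**6. Is it needed?** Two groups were drawn from one distribution with mean 86.4, SD 27.5 and a heavy ceiling, 600 people in all, 10,000 times per split. The distribution had only four levels. It serves as a hard test of the linear model and not as a description of this score.

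| Smaller group | Type I error, ordinary linear comparison | Type I error, unequal-variance (Welch) test |
|---|---|---|
| 50% | 5.2% | 5.2% |
| 10% | 4.8% | 5.7% |
| 5% (30 v 570) | 4.9% | 7.8% |

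The untransformed model holds its level. The unequal-variance test is somewhat liberal when one group is very small.

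**7. Poisson.** With variance/mean ratio φ, the model-based SE is 1/√φ of the true SE, and a nominal 5% test rejects with probability 2 × (1 - Φ(1.96/√φ)). All values of φ are assumptions.

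| φ | SE too small by | Type I error | CI coverage |
|---|---|---|---|
| 1 | 0% | 5% | 95% |
| 1.5 | 18% | 11% | 89% |
| 2 | 29% | 17% | 83% |
| 3 | 42% | 26% | 74% |
| 4 | 50% | 33% | 67% |

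Negative binomial simulations (300 v 300, mean 2 or 3) gave 11.7%, 18.0%, 25.8% and 31.9% for φ = 1.5, 2, 3 and 4 with the Poisson SE. With robust variance they gave 5.1% to 5.6%.

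**The case against.** The strongest reply is that the article lists model families in one sentence. Dispersion checks, robust variance and the choice of transformation usually belong in an analysis plan, which is not shown. Naming Poisson regression does not exclude robust standard errors, and back-transformation is not excluded either. Descriptive summaries are planned as means or medians with no mention of transformation, so comparison of levels with earlier studies can stay on the original scale. This stands as a limit on the point. It does not remove it, because the transformation rule and the choice of Poisson are stated outright, and the first fits the plan's own figures poorly.

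Three stronger readings are tempting and are not supported:

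- **That most participants must sit exactly at the maximum, so that no transformation can help.** This follows if the score has only four levels. The article describes five questions and never a four-level score, and step 5 shows that a finer scale allows a small share at the maximum.
- **That linear regression fails for this outcome.** The simulation shows that it does not. Only the transformation rule is in question. Unequal variance between groups is possible, but the article gives no figure for it.
- **That the counts are known to be overdispersed.** The article gives a reason to expect it for DMFT, namely tooth loss from mixed causes, but no number. For resource use it says only that variation will be analysed, and Poisson is not assigned to it by name.

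It is also fair to say that the planning figures come from a cited study and may not describe the five-question score. The ceiling argument is conditional on that.

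**Conclusion.** The point holds in a limited form. If the planning mean and SD apply to the primary score and its range is 0 to 100, the residual-triggered transformation would very likely come into play. It would make the scale of the primary contrasts depend on the data, with no assurance of curing the skew and no need for it at about 600 people.

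For counts, Poisson with model-based standard errors is a fragile default. The harm ranges from none at a variance/mean ratio of 1 to a 33% rejection rate at an assumed ratio of 4, and the documents do not show where in that range the outcomes lie.

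This is a cheap improvement that should be made before analysis. It is not a fault that undermines the study.

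**What to change.** **Primary score.** Analyse it on its original scale, with no transformation triggered by residuals. Use robust or bootstrap standard errors within the single-level or multilevel models already planned, and add an ordinal model as a sensitivity analysis. Apply a small-sample correction where an exposure group is small, given the 7.8% seen at 30 v 570. Do not rely on uncorrected cluster-robust errors over only 16 centres.

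**Counts.** Make negative binomial regression, or Poisson with robust variance, the default for DMFT and for any resource-use item modelled as a count.

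If an analysis plan already says this, the published rules should be brought into line with it.

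**Cost.** Wording and minor code changes only, with no effect on recruitment or data collection. Confidence intervals for overdispersed counts become wider by √φ, for example 1.22 times at a ratio of 1.5 and 1.41 times at a ratio of 2.

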## Methods and analysis

### Study design and setting

The Cleft@18–23 research clinic work package is a multicentre observational study. Research clinics will take place across sites covering the 16 regional cleft units in the UK (figure 1).

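### For count outcomes such as DMFT, a Poisson model whose only random effect is centre could report centre variation that is really person-to-person spread

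*Protocol article*

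**What the plan says.** Three statements in the Data analyses section of the protocol article work together.

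- Model family: "Linear, logistic, ordinal logistic or Poisson regression will be used to model associations for continuous, binary, ordinal or discrete outcomes, respectively".
- Centre variation: "Potential cleft centre-level variation for each outcome will be identified through estimation of variance partition coefficients from multilevel models". Centre enters these models as a random effect, and no other random effect is named. Age and sex are given as examples of the fixed effects.
- Consequence: "Any outcomes displaying centre-level variation will be modelled using multilevel rather than single-level models".

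The section does not list which outcomes count as discrete. The clear case is in Dental outcomes and oral health: "Dental health will be measured using the sum of the number of Decayed, Missing and Filled Teeth". The number of centres comes from Study design and setting: "Research clinics will take place across sites covering the 16 regional cleft units in the UK". The target of 640 participants is in Power calculations, which also expects some sites to recruit more than others.

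For continuous outcomes the section provides a remedy, transformation, when residuals are skewed. For discrete outcomes it names Poisson regression and no alternative.

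**The concern.** In a linear multilevel model the person-level variance and the centre variance are both estimated, so the VPC divides the total cleanly. In a Poisson multilevel model the person-level variance is not estimated. It is fixed at the mean. If people differ more than that, centre averages also scatter more than the Poisson model expects, even when centres are identical. The centre variance is the only free term that can absorb this extra scatter, so it is biased upwards.

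Overdispersion is plausible for DMFT. Study population admits all cleft subtypes, with and without syndromic diagnoses. The dental section itself notes that many teeth in this population are missing for reasons other than decay. Adjusting for variables such as age and sex would not remove that heterogeneity.

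At stake is a statement that dental health differs between cleft centres. Regional variation is one of the main things this work package sets out to describe, and the programme intends to act on the variation it finds. A false centre signal in a count outcome could misdirect that response.

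**Working it through.** **The plan's own figure.** There is none to reproduce. The article states no VPC, no expected centre variance and no mean or variance for any count outcome.

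**Inputs.** From the article: 16 centres and 640 participants, so 640/16 = 40 per centre on average. Assumed: no true centre effect, counts with mean 2 or 4, and a variance-to-mean ratio φ of 1 (true Poisson), 2 or 4.

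**Check by hand.** Let m be the mean count and n the number of people per centre.

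- With no centre effect, the variance of a centre average is φm/n.
- The Poisson model expects m/n.
- The excess, (φ−1)m/n, is read as centre variance, while the person-level variance is held at m.
- Spurious VPC ≈ [(φ−1)m/n] / [(φ−1)m/n + m] = (φ−1)/(n+φ−1).

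With n = 40:

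- φ = 1: 0/40 = 0
- φ = 2: 1/41 = 0.024
- φ = 4: 3/43 = 0.070

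A similar argument gives an approximate false-positive rate. The Poisson heterogeneity statistic across 16 centres then behaves like φ times a chi-square on 15 degrees of freedom, and its 5% cut-off is 25.0. At φ = 2 the chance of exceeding it is P(χ² > 12.5) = 0.64. At φ = 4 it is P(χ² > 6.25) = 0.98.

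**Simulation.** Negative binomial counts were generated with no centre effect and fitted with a Poisson random-intercept model by adaptive quadrature, 60 datasets per setting. With s² the estimated centre variance on the log scale and m the marginal mean, VPC = m²(exp(s²)−1) / [m + m²(exp(s²)−1)]. The centre variance was tested by a one-sided 5% likelihood-ratio test (cut-off 2.706). The article names no test, so this one is only an illustration. The unequal layout had four centres each of 10, 25, 45 and 80, again 640 in total.

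| Centre sizes | Mean | φ | Mean VPC | Test rejects | VPC above 0.05 |
|---|---|---|---|---|---|
| 16 × 40 | 2 | 1 | 0.002 | 0% | 0% |
| 16 × 40 | 2 | 2 | 0.020 | 50% | 7% |
| 16 × 40 | 2 | 4 | 0.074 | 100% | 78% |
| 16 × 40 | 4 | 1 | 0.002 | 0% | 0% |
| 16 × 40 | 4 | 2 | 0.022 | 60% | 8% |
| 16 × 40 | 4 | 4 | 0.064 | 98% | 60% |
| Unequal | 2 | 1 | 0.001 | 2% | 0% |
| Unequal | 2 | 2 | 0.016 | 35% | 3% |
| Unequal | 2 | 4 | 0.084 | 93% | 70% |
| Unequal | 4 | 1 | 0.001 | 0% | 0% |
| Unequal | 4 | 2 | 0.023 | 53% | 3% |
| Unequal | 4 | 4 | 0.087 | 90% | 70% |

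With 60 datasets per setting the Monte Carlo standard error is at most √(0.25/60) = 0.065, about 6 percentage points. The hand formula and the simulation agree.

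A separate simulation with 16 centres of 40 and mean 4 gave rejection in 28%, 52%, 85% and 97% of datasets at φ = 1.5, 2, 3 and 5. The mean VPCs were 0.012, 0.021, 0.043 and 0.085. For true Poisson counts the figures were 2% and 0.003.

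**The same null situation with a dispersion term.** A negative binomial random-intercept model (16 × 40, mean 4, 60 datasets) gave a mean VPC of 0.002 at φ = 2 and 0.001 at φ = 4. The test rejected in 2% and 0% of datasets, and no VPC exceeded 0.05.

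**The case against.** Five points can be made against the concern.

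**The overdispersion is assumed.** This stands. The article gives no variance for any count, and at φ = 1 the problem disappears. A tooth count also has an upper limit, so very large ratios are unrealistic; for that reason the conclusion rests on ratios of 2 to 4.

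**No test or VPC cut-off is stated.** This also stands. The rejection rates show how easily a false signal arises; they are not the error rate of a rule in the article. The spurious VPC does not depend on any test.

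**Only part of the extra spread reaches the centre term.** Correct. Most stays within centres as unmodelled residual variation, which is why the spurious VPCs are 0.02 to 0.09 and not larger.

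**A false positive merely leads to a multilevel model, a cautious choice.** That is fair for the exposure estimates. But the article also says that the VPC is how centre variation is identified, so the value carries meaning of its own.

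**An analysis plan that is not shown may add a dispersion term.** It may, and this is why the conclusion says could. But the article does not leave the family open: it fixes Poisson for discrete outcomes and applies the VPC to each outcome.

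A reader might also infer that VPCs for binary and ordinal outcomes are distorted by prevalence. The document does not support that. On the latent scale the logistic VPC is s²/(s² + π²/3), which does not contain the prevalence. With s² = 0.2 it is 0.057 throughout. Only a response-scale VPC moves with prevalence, and the choice of scale is ordinary analysis-plan detail.

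Nor does the article plan to rank or compare outcomes by their VPCs. The Poisson VPC does rise with the mean, but that matters only for a comparison the article does not propose.

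**Conclusion.** The concern holds for count outcomes and is conditional. If counts such as DMFT are overdispersed, the stated combination of Poisson regression and a VPC with centre as the only named random effect could report centre variation where there is none. For 16 centres of about 40 and an assumed variance-to-mean ratio of 2 to 4, the mean spurious VPC is about 0.02 to 0.09. The illustrative 5% test then rejects in about 35% to 100% of datasets, against 0% to 2% for true Poisson counts.

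The reach is limited. The primary outcome is an SF-36 subscale score, for which the linear-model VPC is sound, and other continuous outcomes are likewise unaffected. DMFT is the only clear count outcome. Resource use has its own sentence in Data analyses with no Poisson model named, so it should not be assumed to share the problem. It would be too strong to say that false centre differences will be reported, or that the study's main result is at risk.

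**What to change.** In Data analyses, state that for count outcomes the centre model will include a person-level dispersion term: a multilevel negative binomial model, or a Poisson model with a person-level random effect alongside the centre effect. Report the between-centre variance or SD with its 95% CI before describing an outcome as showing centre variation.

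The cost is one or two sentences and one extra parameter per count model. No new data are needed. Some centre variation that a plain Poisson model would have shown will disappear.

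### Centre clustering is modelled only for outcomes that show it, so a region-level contrast can get too small a standard error when modest clustering is missed

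*Protocol article*

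**What the plan says.** The article plans single-level regression (linear, logistic, ordinal or Poisson) of each outcome on each exposure, before and after adjustment. On centres, Data analyses first says: "Potential cleft centre-level variation for each outcome will be identified through estimation of variance partition coefficients from multilevel models", with centre as a random effect and adjustment for fixed effects such as age and sex. It then sets the rule: "Any outcomes displaying centre-level variation will be modelled using multilevel rather than single-level models". Outcomes that do not display such variation keep the single-level model. No test, interval or VPC cut-off is named.

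Study design and setting gives the number of clusters: "Research clinics will take place across sites covering the 16 regional cleft units in the UK". Power calculations expects them to differ in size: "Some serve a larger population than others, so it is likely that we may recruit more from some sites than others". Geographical location is one of the listed exposures and is part of the primary research question at the end of the Introduction. Whether it means centre, region, nation or place of residence is not stated.

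**The concern.** Not seeing centre variation in a sample is weak evidence that there is none, and here that observation chooses the error structure for the inference that follows from the same data. With 16 centres, a small VPC can easily go unseen. The outcome then gets a single-level model that treats participants from one centre as independent.

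The loss falls mainly on exposures that are constant within a centre. If geographical location is analysed as region or nation, its standard error depends on the between-centre variance, which is what the single-level model drops. Geographic results for different outcomes would also rest on different error structures, which makes them harder to compare.

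**Working it through.** **Inputs from the article.** 16 centres; 600 analysable participants (target 640); unequal centre sizes expected. Average size m = 600/16 = 37.5.

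**Assumptions.** The article gives no VPC, so 0 to 0.10 is used. The criterion for displaying variation is not stated, so three readings are tried. The region-level exposure is taken as binary with no true effect, splitting centres 8 v 8.

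**The plan's own figure.** The article states: "A sample of 600 would allow a mean score of 86.4 to be estimated with a 95% CI of 84.2 to 88.6". The half-width is (88.6 - 84.2)/2 = 2.2. The SD is not printed; solving 2.2 = 1.96 x SD/√600 gives SD = 2.2 x √600/1.96 = 27.5. This only inverts the stated figure and does not test it. It does show that the formula has no term for clustering.

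**Step 1: chance of detecting centre variation.** For equal centres the random-effects F-test has 15 and 584 df and a 5% critical value of 1.684. Power = P(F > 1.684/[1 + 37.5ρ/(1 - ρ)]). For ρ = 0.01, the divisor is 1 + 37.5 x 0.01/0.99 = 1.379, and P(F > 1.221) = 0.25.

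**Step 2: size of the standard-error shortfall.** DEFF = 1 + (37.5 - 1)ρ. For a centre-level exposure the single-level standard error should be multiplied by √DEFF. If clustering were always ignored, type I error would be 2P(Z > 1.96/√DEFF).

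| VPC | Detected, 5% F-test | DEFF | √DEFF | Type I error if clustering always ignored |
|---|---|---|---|---|
| 0.01 | 25% | 1.37 | 1.17 | 9.3% |
| 0.02 | 50% | 1.73 | 1.32 | 13.6% |
| 0.03 | 70% | 2.10 | 1.45 | 17.6% |
| 0.05 | 90% | 2.83 | 1.68 | 24.4% |
| 0.10 | 99% | 4.65 | 2.16 | 36.3% |

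A boundary likelihood-ratio test in simulation gives similar detection rates: 22%, 46%, 67%, 88% and 99%.

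**Step 3: type I error under the rule itself.** This used 4,000 simulated studies per setting, with 600 participants in 16 centres of equal size or ranging from 11 to 64. The random intercept was fitted by REML. Multilevel fits used t on 16 - 2 = 14 df; single-level fits used the normal reference. Entries are equal / unequal centre sizes.

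| VPC | Switch at p<0.05 | Switch at VPC > 0.05 | Switch at any non-zero VPC | Multilevel always |
|---|---|---|---|---|
| 0 | 4.3 / 4.1% | 4.9 / 4.7% | 2.9 / 2.7% | 2.3 / 2.3% |
| 0.01 | 6.8 / 7.0% | 9.5 / 10.3% | 4.0 / 4.4% | 3.7 / 4.3% |
| 0.02 | 6.3 / 7.8% | 11.9 / 14.4% | 4.2 / 5.3% | 4.2 / 5.1% |
| 0.03 | 5.4 / 6.3% | 13.0 / 14.4% | 4.3 / 4.6% | 4.2 / 4.5% |
| 0.05 | 6.0 / 6.3% | 13.4 / 14.1% | 5.3 / 5.6% | 5.2 / 5.6% |
| 0.10 | 5.2 / 5.5% | 6.7 / 7.3% | 5.1 / 5.4% | 5.1 / 5.4% |

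With a normal reference in place of t on 14 df, the p<0.05 switch gives 4.2-8.8% and the always-multilevel model 3.8-7.8%. The small-sample degrees of freedom therefore matter as well as the centre term.

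**Step 4: individual-level exposures.** A binary exposure analysed by single-level regression throughout, at VPC 0.02 and 0.05, gives 5.3-5.6% when it is evenly spread over centres. When its prevalence varies strongly between centres (SD 0.20), it gives 6.4-7.1%.

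**The case against.** A reader might infer that 16 centres cannot support any decision about clustering. The figures do not bear that out: a VPC of 0.05 is found about 90% of the time and 0.10 about 99%. The weakness is confined to small values.

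A reader might also take the 9%, 14% and 18% in Step 2 (VPC 0.01 to 0.03) as the plan's error rates. They describe always ignoring clustering, which the plan does not do.

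Nor does the article show that every geographic result has a wrong standard error. If geographical location means the cleft centre, the VPC is itself the geographic result, it is estimated for every outcome, and the standard-error argument does not apply in that form. Sex, gender, ethnicity and socioeconomic status are individual-level exposures, for which the effect is small or negligible.

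The criterion may be set in an analysis plan that is not shown, so its absence is no fault. If any non-zero estimate counts as displaying variation, the rule fits nearly the same models as the fix. Under a p<0.05 criterion, the excess over always using the multilevel model is about 1 to 3 percentage points at VPC 0.01 to 0.05.

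All of this stands and limits the size of the point. It does not remove it: the article makes the model conditional on what the data show, and any criterion that sometimes drops a real centre effect carries some of this cost.

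**Conclusion.** The concern holds in a limited form. The rule lets the data choose, per outcome, whether clustering enters the model, and with 16 centres it will often miss a VPC of 0.01 to 0.02, where the design effect is already about 1.4 to 1.7. For a contrast above centre level, type I error is about 6-8% at those VPCs under a p<0.05 switch. It is about 9-14% for VPCs of 0.01 to 0.05 under a 5% VPC cut-off, and close to 5% if any non-zero VPC triggers the multilevel model. Evenly spread individual-level exposures are barely affected; those whose prevalence differs strongly between centres are slightly affected.

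These sizes rest on the assumed VPCs, the three readings of the criterion, the 8 v 8 exposure and a continuous outcome. The point matters for the geographic part of the primary question only if geography is analysed at region or nation level. It is worth changing because a fixed rule is better and nearly free.

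**What to change.** Replace the conditional sentence with: 'All regression models, unadjusted and adjusted, include a random intercept for centre whatever the estimated VPC. Linear models use REML with Kenward-Roger or Satterthwaite degrees of freedom. For logistic, ordinal and Poisson models, region-level contrasts use a t reference with between-centre degrees of freedom.'

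Report each outcome's VPC with a confidence interval as a finding, not as a switch. State the unit of geographical location. If it is the centre itself, the VPC and the centre estimates are the geographic result, and centre should not also be entered as a fixed exposure.

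The cost is a change of wording. A random-centre model is already planned for every outcome, and where the centre variance is estimated as zero the fit reduces to the single-level one. Confidence intervals for region-level contrasts become somewhat wider. With no true centre variation, the test is mildly conservative (type I error about 2-3% with t on 14 df).
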